# Summary of Proposed Research

The primary goal of the proposed Community Responses (CR) program evaluation will be to determine the extent to which the United States Agency for International Development (USAID)/South Africa-funded CR program (and particularly the effects of community-based HIV/gender-based violence (GBV) prevention programming, which include a component to create demand for related services) is effective at reducing HIV and sexual and GBV risk, and improving related service utilization. Key outcomes to be measured include:

- Increased uptake of HIV and GBV services [e.g., HIV testing and counseling (HTC), sexual and gender-based violence (SGBV) support services]
- Improvements in sexual risk behaviors
- Reduction in experience/perpetration of SGBV
- Decreased support for harmful gender norms

Project SOAR proposes a cluster randomized stepped-wedge evaluation design, in which clusters are randomized to when they initiate the CR intervention. A cohort of adult men aged 18–35 years and women aged 18–24 years in the evaluation communities will be followed over the course of approximately 32 months, with a baseline survey and three follow-up interviews at approximately ten month intervals. The evaluation will be conducted in selected informal settlements in eThekwini and Ugu in KwaZulu-Natal Province, one of four provinces where the CR program is being implemented.

We will supplement this information with an analysis of District Health Information System (DHIS) data, indicating trends in service utilization, and risk/prevention behaviors, where feasible.

In addition, we will conduct implementation science research to explore the experience of updating and scaling up the Stepping Stones intervention for men and women in informal settlements. This will include qualitative interviews with program implementers, and a selection of study participants.

Overall, this study offers the opportunity to contribute to several critical domains of interest for PEPFAR and the wider HIV and AIDS community. It will assess the effectiveness of a community-based HIV prevention program designed to promote uptake of HIV and SGBV services and transform gender norms to create an enabling environment for HIV prevention behaviors among adult men and women. Building the global evidence base on these questions is vital to both improved outcomes related to HIV prevention and eliminating harmful gender norms, which are linked to a range of other outcomes of concern. These findings will be particularly relevant for the South African context, given the generalized epidemic setting and high levels of reported GBV.

# Background and Rationale

South Africa’s National Strategic Plan (NSP) on HIV and AIDS, sexually transmitted infections (STIs), and tuberculosis (TB) for 2012–2016 sets out four strategic objectives: (1) addressing social and structural barriers that increase vulnerability to HIV, STI, and TB infections; (2) preventing new HIV, TB, and STI infections; (3) sustaining health and wellness; and (4) increasing the protection of human rights and improving access to justice (South African National AIDS Council 2011). The CR program aims to address the first two objectives.

## Addressing social and structural barriers that increase vulnerability to HIV

Gender norms are associated with a host of sexual and reproductive health outcomes and risk behaviors, such as condom and contraceptive use, even after controlling for other factors (Tang et al. 2001; Stephenson et al. 2012; Karim et al. 2003). Gender norms are also closely tied to other antecedents of HIV infection, especially intimate partner violence (IPV) and power in sexual relationships. Inequitable gender norms and traditional masculinity norms have been associated with female IPV victimization (Gomez et al. 2011), and male perpetration of IPV or rape (Gomez et al. 2011; Shannon et al. 2012). The consistency of such findings—across countries, continents, class, and race—is striking. A growing body of evidence suggests that programs that seek to change harmful gender norms can improve health behaviors and outcomes such as number of sex partners, consistency of condom use, STIs, and IPV (Jewkes et al. 2008; Pulerwitz et al. 2015). These programs often focus on convening small groups of participants and engaging them in learner-centered and interactive activities that foster critical reflection about gender norms and inequality, and may complement these with broader behavior change communication activities (Dworkin et al. 2013; Pulerwitz et al. 2010; Pulerwitz et al. 2012).

## Preventing new HIV infections

Utilization of HIV testing services, and linkages to care and treatment for those who test positive, are of critical interest, both because of the promise these hold for reducing HIV transmission and for connecting consumers to the broader health system to improve their treatment outcomes. In the most recent South African National HIV Prevalence, Incidence and Behaviour Survey (Shisana et al. 2014), more than 90% of the population reported knowing where to get an HIV test, while only 65% had ever been tested. In fact, national survey data demonstrated that 62% of men and 45% of women testing positive were unaware of their infection status. Increasing the proportion of the population who are aware of their status can have an immediate impact on treatment uptake and prevention of new infections (Shisana et al 2014).

## Expected results

This study offers the opportunity to contribute to several critical domains of interest for PEPFAR and the wider HIV and AIDS community, as well as addressing HIV program challenges of great relevance for the South Africa context. It will assess the effectiveness of a community-based HIV prevention program designed to promote uptake of HIV and SGBV services and transform gender norms to create an enabling environment for HIV prevention behaviors among adult men and women. The study will also contribute to important questions of how much intervention (dose) is needed to achieve key outcomes.

Further, this research will provide evidence on the experience of implementing a scaled-up version of Stepping Stones in informal settlements (implementation science). There are many outstanding questions about how to best roll-out/scale up this intervention, which has demonstrated evidence of impact in controlled environments. In this case, Stepping Stones is being applied with a reduced number of sessions (than those rigorously evaluated in the past, to permit more wide spread roll out), and with implementing partners that have not worked much with the intervention before.

Building the global evidence base on these questions is vital to both improved outcomes related to HIV prevention and eliminating harmful gender norms, which are linked to a range of other outcomes of concern. These findings will be particularly relevant for the South African context, given the generalized epidemic setting and high levels of reported gender-based violence.

# Intervention Description

## The Community Responses (CR) program

The United States Agency for International Development (USAID)/South Africa is supporting the five-year Community Responses (CR) program (2014-2019), implemented by the Centre for Communication Impact (CCI). The target population for the CR program is young men (ages 15–35) and women (ages 15–24)^[[1]](#footnote-2)^ living in informal settlements in the United States President’s Emergency Plan for AIDS Relief (PEPFAR) communities, located in 23 sub-districts within the Gauteng, Kwazulu-Natal, Western Cape, and Mpumalanga provinces.

The CR program includes the following reinforcing components:

1. *Standardized HIV prevention interventions* (PP_PREV),^[[2]](#footnote-3)^ defined as interventions that are designed for a specific priority population to reduce HIV transmission, implemented the same way each time, adhere to written protocols, include goals and activities tailored to the priority population, comprise multiple encounters with the same individuals or small groups, and have a system for tracking and reporting the completion of every element of the intervention. Specific interventions include ZAZI^[[3]](#footnote-4)^ and Brothers for Life (1x2 hour sessions).^[[4]](#footnote-5)^ Participants will be encouraged and referred for services including: HIV testing and counseling (HTC), voluntary male medical circumcision (VMMC), prevention of mother to child transmission of HIV (PMTCT), contraception, condoms, antiretrovirals (ARVs); uptake and adherence), and sexual and gender-based violence (SGBV).
2. *Structural interventions (SI) for gender norms for HIV and gender-based violence (GBV) prevention* (GEND_NORM),^[[5]](#footnote-6)^ are defined as interventions that support participants to understand and question existing gender norms and reflect on the impact of those norms on their lives and communities; make a clear link between the gender norms being discussed and HIV prevention, treatment, care or support; and have a minimum of 10 hours contact time per individual. Specific interventions will include grassroots soccer/SKILLZ curriculum^[[6]](#footnote-7)^ (in-school youth aged 15–19), and Stepping Stones for youth and adults aged 20 and older.^[[7]](#footnote-8)^ Participants will be encouraged and referred for services including: HTC, VMMC, PMTCT, contraception, condoms, ARVs (uptake and adherence), and SGBV and post-exposure prophylaxis (PEP) services.
3. *SGBV prevention activities:* These are defined as interventions that raise awareness of SGBV and increase knowledge and access to PEP; promote and refer to local SGBV service providers, where they exist; refer to the South African Police Services, psychosocial support services, and relevant government departments; and emphasise networks, key stakeholders, and service providers to ensure joint implementation and effective referrals. Specific interventions will include: community dialogues focused on SGBV prevention and workshops for men (10x1 hour sessions).
4. *Community dialogues*: The CR program will also include situational analyses and mapping activities before interventions begin, and will provide feedback on community achievements after interventions. Community dialogues will take place in all CR communities.

The CR program was designed to align with the Government of South Africa’s National Strategic Plan for HIV, sexually and transmitted infections (STIs), and tuberculosis (TB) (NSP) for 2012–2016, as well as with the UNAIDS targets for 2020: 90% of people living with HIV knowing their status, 90% of those who know their status on ART, and 90% of those on antiretroviral treatment (ART) virally suppressed (90:90:90 target).^^[[8]](#footnote-9)^^

# Research and Evaluation

## Goals and objectives

The overall goal of this research is to generate and disseminate evidence regarding community-based interventions aiming to prevent HIV transmission and reduce GBV (and increase HIV/GBV service use) among adult men and women in a high prevalence setting. Specifically, the CR evaluation has the following primary and secondary objectives:

***Primary objective:*** Conduct an **impact evaluation to** assess the effect of the CR program on key outcomes for adult men and women living in communities exposed to the CR program, compared to those living in control communities, on key program outcomes.

- The primary analyses, based on an intent-to-treat approach, will compare at the community or cluster level the average change in outcomes after full CR program exposure to the average change in outcomes in communities that have not yet received the CR intervention.
- Additional analyses will also assess whether individual or community-level program exposure (e.g., proportion of the community that participated in each component) leads to improvements in key program outcomes on an as-treated basis.^^[[9]](#footnote-10)^^
- Further, analyses of district health information software (DHIS) data from health facilities in program catchment areas will also be used to assess trends in service utilization for key HIV and SGBV services.

***Secondary objectives:*** Conduct **implementation science research** to assess participant perspectives and experiences with the Stepping Stones component of the CR program, as well as to provide a deeper understanding of the implementation process and reasons for program effectiveness. As part of this effort, we will conduct:

- Qualitative analysis of in-depth interviews (IDIs) and focus group discussions (FGDs) with a subset of program participants to learn about their experiences and recommendations regarding the program.
- Qualitative analysis of IDIs and FGDs with program staff to discuss the process, experiences, challenges, recommendations, and benefits of implementing (and scaling up) the current version of Stepping Stones, as well as updating information related to current treatment (and treatment as prevention) guidelines.
- Direct observations of a limited selection of Stepping Stones meetings to assess the fidelity of program implementation to program design, the ability of the facilitators to convey core information and to foster interactive sessions, and the responsiveness of the participants to the material and sessions.

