**Table 2. Illustrative schedule of program rollout and survey (32 months total)**

| **Beginning of period** | | **Aug 2016** | **Oct**  **2016** | **June 2017** | **Aug 2017** | **May 2018** | **June 2018** | **Feb 2019** |
| --- | --- | --- | --- | --- | --- | --- | --- | --- |
| Length of period (months) | | 2 | 8 | 2 | 8 | 2 | 8 | 2 |
| **Group A**  *(6 clusters)* | Survey | BL |  | R2 |  | R2 |  | R4 |
|  | Program rollout/ implementation |  | R | I | I | I | I | I |
| **Group B**  *(6 clusters)* | Survey | BL |  | R2 |  | R3 |  | R4 |
|  | Program rollout/ implementation |  |  |  | R | I | I | I |
| **Group C**  *(6 clusters)* | Survey | BL |  | R2 |  | R3 |  | R4 |
|  | Program rollout/ implementation |  |  |  |  |  | R | I |

**Notes**: In each time period, we assume two months for data collection followed by eight months for program implementation. “BL, R1, R2, R3, R4” indicates data collection; “R” indicates rapid program rollout after the respective survey has been completed; “I” indicates ongoing program implementation in the specified groups during the indicated time periods. Blank cells in the “program rollout/implementation” rows indicate that those communities will act as comparison groups during those periods.

There are several key requirements of this evaluation approach, which have important implications for implementation of the CR program:

1. *Randomized rollout of CR activities in evaluation communities*: CR activities will be rolled out randomly (at eight month intervals) within a pre-determined subset of CR communities. SOAR will work with CCI to randomize the schedule of rollout, and CCI will not initiate any program activities before rollout is scheduled for the community.
2. *Rapid rollout and saturation of all CR activities once program commences in each area*: The full package of CR activities will begin quickly throughout each community when that community’s implementation period begins. Also, the full package of CR activities should saturate each community quickly after the program commences in each cluster.
3. *Avoid contamination across clusters*: Clusters will be selected as to avoid contamination across clusters. Geographically separate clusters will be identified and the evaluation team will work with CCI to assure that the program does not cross-over into areas that are not yet scheduled for the intervention.

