While the primary analysis and impact assessment will rely on an ITT approach, it will nonetheless be interesting to evaluate whether actual participation in the CR program predicts outcomes differentially if participation in the intervention is not 100%. It is important, however, to recognize the statistical estimation problems that result from selection into the program based on factors that can be/are measured and/or by unobservable factors. The central problem is that factors affect both participation in the program and outcomes and behaviors of interest leading to biased estimates of program impact if selection is not considered. To address these limitations, multiple estimation approaches will be explored. The first will be an instrumental variables regression, in which a model of program participation will be estimated using observed covariates and known exogenous variables, such as the original randomization period, and whether the participant was randomly chosen to receive program promotional material and outreach. A second approach will use fixed effects models that effectively control for the all unobserved constant influences from individual, family, and community characteristics.

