6. SKILLz is a lifeskills and sexual reproductive health curriculum that provides young boys and girls 12–18 knowledge and decision making around HIV prevention, discrimination, stigma, HIV testing and access to treatment. [↑](#footnote-ref-7)
7. Stepping Stones is a program in which community members are engaged in interactive sessions covering topics on gender, HIV, communication and relationships skill building. In addition, Stepping Stones addresses issues of gender norms, gender-based violence and intimate partner violence. [↑](#footnote-ref-8)
8. Center for Communication Impact, “USAID Community Responses: Overview of the CR Programme.” Sub-partner Inception Meeting. 12 November 2015, South Africa. [↑](#footnote-ref-9)
9. Conducting “as treated” analyses on an individual-level will require use of appropriate study design and statistical approaches for handling self-selection into program exposure groups, e.g., random promotion or instrumental variable analysis. [↑](#footnote-ref-10)
10. Statistical power in stepped-wedge design trials depends on the number of clusters, the number of randomization times, and the number of clusters randomized at each time point; increasing the overall number of measurement times (i.e., randomization times) increases power. Power is also affected by amount of time needed for full effect of program; that is, if the full effects are not realized in the first time period in which it is implemented, power will be further reduced (Hussey & Hughes 2007). [↑](#footnote-ref-11)
11. Wards are geopolitical subdivisions of municipalities. Although defined largely for electoral purposes, wards are a geographic level of demarcation use by the South Africa National Census. [↑](#footnote-ref-12)
12. Google Earth provides high resolution satellite images of at least 15 meters per pixel of resolution, providing relative clear demarcations of structures and landmarks. Most images of the informal settlements and environs in South Africa are from 2016 and, hence, up-to-date. [↑](#footnote-ref-13)

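### Community coverage of each CR component is to be assessed for its effect, but all components start together, so randomization identifies only the effect of the whole package

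*Protocol*

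**What the plan says.** The primary objective (protocol, Goals and objectives) is an intent-to-treat comparison of the whole program. Additional analyses then ask whether individual or community-level exposure ("e.g., proportion of the community that participated in each component) leads to improvements in key program outcomes on an as-treated basis"). The coverage data are to come from program monitoring, which will track the percentage of residents engaging in the different components (Routine program monitoring data).

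Four components are listed under The Community Responses (CR) program, introduced with "The CR program includes the following reinforcing components". For the last of them, "Community dialogues will take place in all CR communities".

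On timing, requirement 2 below Table 2 states that "The full package of CR activities will begin quickly throughout each community" and that "the full package of CR activities should saturate each community quickly after the program commences in each cluster". No component is randomized or staggered separately.

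Two places deal with as-treated bias. Footnote 9 says such "analyses on an individual-level will require use of appropriate study design and statistical approaches for handling self-selection". The Statistical analysis plan section proposes instrumental variables, in which "a model of program participation will be estimated using observed covariates and known exogenous variables, such as the original randomization period", together with random promotional outreach, and also fixed effects models. These address selection into participation. Neither addresses how to separate components that are switched on at the same moment.

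**The concern.** Randomization in this design decides one thing per cluster: when the package starts. Before that, coverage of every component is zero; afterwards, all are expected to be above zero. In a model holding one component's coverage, that variable is therefore mainly an indicator that rollout has happened, and it picks up whatever the package does. What distinguishes components at community level is how uptake happened to differ among 18 clusters, which nobody randomized.

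The stated remedies do not supply what is missing. The rollout period moves all components at once. The random outreach described for survey participants is a general invitation to events and programs; Stepping Stones is named as an example, but no separate randomization by component is set out. Fixed effects remove constant cluster differences and leave the common switch in place.

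At stake is a statement in the results that a particular component improves outcomes when the design can support that only for the package.

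**Working it through.** **1. The plan's own figure.** Inputs from Power and sample size calculations: 18 clusters, 6 crossing per step, 4 rounds, 35 per sex per cluster, ICC 0.05, 45% baseline, 10-point effect, alpha 0.05 (taken as two-sided), power 0.80. With K=18 and T=4, the exposure pattern gives U=18+12+6=36 exposed cluster-rounds, W=0²+6²+12²+18²=504 and V=6×(3²+2²+1²)=84. Total variance is 0.45×0.55=0.2475, so τ²=0.05×0.2475=0.012375 and σ²=0.95×0.2475/35=0.006718.

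The Hussey-Hughes variance is Kσ²(σ²+Tτ²) / [(KU−W)σ² + (U²+KTU−TW−KV)τ²].

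- Numerator: 18×0.006718×0.056218 = 0.006798
- Denominator: 144×0.006718 + 360×0.012375 = 5.4224
- SE = √0.0012537 = 0.0354; power = Φ(0.10/0.0354−1.96) = 0.806

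Thirty-five is the smallest cluster size reaching 0.80, giving 18×35=630 per sex and 1,260 in total. 1,260/0.85=1,483, against the stated 1,500. The plan's figure reproduces.

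**2. Why the instrument cannot separate components.** With randomized exposure as instrument, the estimate for component k is the package effect on the outcome divided by the rollout effect on coverage of k. At mean coverage 0.5 this is 0.10/0.5=0.20 for the active component, and also 0.10/0.5=0.20 for an inert one. The test is nearly the intent-to-treat test whichever component is named.

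**3. Simulation on the same design** (one sex, total variance 0.25, 3,000 runs per setting). One component carries the whole 10 points and one is inert. The protocol gives no coverage mean, spread or correlation, so these are assumed. A component is credited when it is significant in the beneficial direction. The joint columns have both components in one model; +R adds the rollout indicator.

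| Mean | SD | Corr. | Alone: active / inert | Joint: active / inert | Joint + R: active / inert |
|---|---|---|---|---|---|
| 0.5 | 0.05 | 0 | 83% / 80% | 10% / 3% | 6% / 3% |
| 0.5 | 0.10 | 0 | 84% / 76% | 26% / 2% | 16% / 3% |
| 0.5 | 0.10 | 0.5 | 86% / 82% | 16% / 3% | 14% / 3% |
| 0.5 | 0.20 | 0 | 92% / 63% | 69% / 2% | 46% / 2% |
| 0.5 | 0.20 | 0.5 | 92% / 81% | 44% / 3% | 36% / 3% |
| 0.3 | 0.10 | 0.5 | 90% / 83% | 33% / 3% | 29% / 3% |
| 0.3 | 0.20 | 0 | 98% / 52% | 94% / 2% | 81% / 2% |

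At correlation 0.8 the inert component fitted alone is credited in 81-94%, and joint power is 5-44%. With the instrument (mean 0.5), the active component is credited in 79-80% and the inert one in 76-80%, against 80-81% for intent-to-treat.

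The cause is collinearity. Net of cluster and round, the two coverage columns correlate 0.97-0.99 at SD 0.05, 0.90-0.95 at SD 0.10 and 0.70-0.85 at SD 0.20 (mean 0.5, correlation 0-0.5).

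**4. What the joint model assumes.** The 2-3% holds because simulated uptake was unrelated to anything else about the cluster. If clusters that take up the inert component more also respond more to the package, false credit rises to 32-49% in the cases run. How far it rises depends on the assumed strength of that link, which the protocol gives no means of fixing.

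**The case against.** The strongest reply is that the protocol promises little here. Component coverage stands inside an example, in an additional analysis, and the Statistical analysis plan section speaks of participation in the program, not in its parts. A reader might infer that the evaluation will judge or rank every component and so decide which are scaled up. The text does not say so: no passage ranks components, and its scale-up questions sit mainly with the implementation science work. That part of the reply stands.

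A reader might also infer that an inert component will be credited almost as often as the active one however the data are modelled. That does not follow either. The high rates need one-at-a-time fitting or the randomization instrument, and the protocol does not fix the model for component coverage; a separate analysis plan may. In a joint model the rate is nominal under the condition given above. With wide, independent coverage the gap is also large even one at a time (98% against 52%).

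Third, individual participation varies within clusters, and components reach different people: Stepping Stones is for those aged 20 and older, for instance, and some workshops are for men. The calculation covers community-level coverage only.

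What survives is the mismatch between the claim and the design. Choosing another model exchanges false credit for usually low power and for reliance on non-random uptake. No model creates randomization by component.

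**Conclusion.** The point holds in limited form. The protocol attaches causal wording to coverage of each component, while its rollout rule lets randomization identify only the package.

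Under the assumed means, SDs and correlations up to 0.5, an inert component fitted alone is credited in about 50-82% of trials, against about 82-98% for the active one; with the instrument, both are near 76-80%. Jointly, false credit is nominal only if uptake differences between clusters are unrelated to outcomes. Power for the active component is mostly about 5-50%, and higher only where coverage varies widely relative to its mean without being strongly correlated between components. These ranges rest on assumed coverage, since the protocol gives none.

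A reader might take this as a threat to the main result. It is not: the primary analysis compares randomized exposure to the whole program and does not use coverage.

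**What to change.** In Goals and objectives, limit the causal as-treated statement to exposure to the CR package as a whole, with randomized rollout as the instrument, as the Statistical analysis plan section already allows. This is largely the intent-to-treat effect rescaled by coverage, so it should be presented as that and not as independent evidence.

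Where component coverage is analysed, enter all components together with the rollout indicator, cluster effects and round effects. Report the coefficients as descriptive associations, state that randomization does not identify them because the components start together, and drop the causal verb for single components.

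The cost is a change of wording and a model on data already to be collected. What is given up is component-specific causal claims that the design cannot support.
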